## Background

Intrahepatic cholestasis of pregnancy (ICP) is the most frequent liver disorder specific to pregnancy, with an annual Australian incidence of 0.6–0.8% [1]. Its cardinal features are maternal pruritus and increased serum bile acids (BA), commonly towards the end of the third trimester. The pruritus, though often mild, can occasionally be extremely severe, causing major skin excoriations, profound sleep disturbances and associated psychopathology, with iatrogenic premature delivery for symptom relief. ICP can also cause severe liver dysfunction and jaundice. BA are formed in the liver and secreted in the bile into the intestine, where they emulsify fat in the ingested food and enable its uptake into the liver, where the BA are recycled. In ICP, this cycle of “enterohepatic circulation” is inhibited and serum BA concentrations increase, providing a marker for the disorder [2]. Increased rates of postpartum haemorrhage (PPH) reported in early studies [3] have not been confirmed in more recent larger datasets [4]. Gallstones may be present more often in these women [5]. Women with hepatitis C infection have a higher incidence of ICP [6]. Maternal symptoms typically resolve after birth, but affected women have an increased risk of hepatobiliary disease in later life [6]. There are few data for long term outcome in the children of mothers with ICP [7].

ICP has been associated with increased fetal risks, including spontaneous preterm birth, fetal hypoxia and compromise (including meconium-stained liquor) and unexpected intrauterine fetal death [3]. Higher concentrations of circulating BAs are associated with increased fetal risks, including spontaneous preterm birth, asphyxial events and stillbirth [8, 9]. Early onset (less than 34 weeks gestation) severe (defined as serum BA > 40 μmol/L) ICP is a rare disorder with an Australian incidence of 0.1% per annum [1].

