Miscarriage (fetal death before 20^+ 0^ weeks gestation)Stillbirth (death before delivery ≥20^+ 0^ weeks gestation or > 400 g if gestation unknown)Neonatal death in hospital up to 7 days after birth (excluding death due to congenital anomalies)Neonatal unit admissions until infant discharge home from hospitalNumber of nights in each category of care (intensive, high dependency, special, transitional and normal) and total number of nights in hospitalBirth weight (g), and customised/population birth weight centile (GROW) [33]Apgar scores at 1 and 5 min after birthUmbilical arterial and venous pH (and base excess) at birthCord blood BANeed for supplementary oxygen prior to discharge, and number of days when such oxygen is requiredNeed for ventilation support (continuous positive airway pressure - CPAP/high flow/endotracheal ventilation)Pneumothorax (confirmed on chest X-ray)Need for phototherapyAbnormal cerebral ultrasound scanConfirmed sepsis (positive blood or cerebrospinal fluid cultures)Necrotising enterocolitis (Bell’s stage 2 and 3)Seizures (confirmed by EEG or requiring anticonvulsant therapy)Encephalopathy grade (worst at any time: mild, moderate, severe)Hypoglycaemia (blood glucose < 2.6 mmol/l on two or more occasions)Severe hypoglycaemia (blood glucose < 1.8 mmol/l on two or more occasions)Other indications and main diagnoses resulting in NNU admission.Mode of feeding at discharge from hospital

The primary outcome, maternal pruritus score, will be evaluated at 1 week after trial entry and then on a monthly basis up to 28^+ 0^ weeks gestation and then weekly to delivery.

The timepoints of evaluation of the secondary maternal outcomes are at 1 week post-randomisation visit, at monthly clinic visits at 20, 24 and 28 weeks gestation (if randomised prior to that), at weekly clinic visits after 28 weeks gestation and during admission for birth, and of the secondary neonatal outcomes at delivery and 1 week and 6 weeks after birth.

The following information post enrolment will be captured for health resource use:
Maternal: total number of nights (antenatal, intrapartum and postnatal) together with level of care including adult ICU.Infant: total number of nights for the baby in neonatal unit, together with level of care (e.g. neonatal ICU).

The costs of UDCA and rifampicin, together with the costs of any additional treatment, will be calculated in both the UDCA and rifampicin groups.

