### Subsequent visits

At the first visit a week after randomisation, and then at least monthly, if randomised prior to 28 weeks gestation, and then weekly thereafter, the woman is asked for a value of the worst itch she felt during the previous 24 h, which is then scored on the itch chart. Serum is drawn and monitored for measurement of BA and liver biochemistry and measurement of prothrombin time and activated partial thromboplastin time (as per usual clinical practice), together with any further biological samples for later assessments (with the woman’s consent) under separate protocols, together with routine cardiotocography and ultrasound monitoring (weekly umbilical artery Doppler, 2-weekly growth parameters). The dose of treatment is altered at the discretion of the responsible clinician.

If maximal doses of primary drug therapy are reached, consideration is given to the addition of, first UDCA or rifampicin respectively, following measurement of any appropriate biochemical and microbiological samples, to enable the relevant comparisons to be drawn, and then other therapy, eg cholestyramine, in addition to the trial therapy.

Women in the study, whether randomised to either UDCA or rifampicin, who develop steatorrhoea, are also to be prescribed vitamin K supplements (10 mg daily) to be taken until delivery.

Women may be prescribed pre-delivery antenatal steroids for enhancing lung maturity at the discretion of the treating clinician. Any such antenatal steroid therapy will be recorded in the eCRF.

The remainder of antenatal care and, in particular, decisions about the mode of birth as well as the administration of steroids for promotion of fetal lung maturity, is left to the discretion of the treating clinician. All neonates, and especially those of women taking rifampicin, are to be given parenteral Vitamin K at birth.

The post-delivery outcome will be completed after delivery and before the woman leaves hospital.

Participants will be asked to attend for follow-up at 6 weeks postpartum, with routine blood samples (including BA measurement as well as OGTT, if appropriate) collected 1–3 days beforehand.

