### Expected events

The following are considered as expected occurrences in this population of pregnant women or a result of the routine care/treatment of a participant. As such, they will be recorded on the eCRF but not reported as AEs or SAEs:
Worsening pruritusHospitalisation for worsening ICPGestational diabetes/diabetes stabilisationPre-eclampsiaAdmission in active labourAdmission for cervical ripening or induction of labourAdmission for caesarean sectionShort term (< 24 h) admission for assessment for suspected fetal compromise, including reduced fetal movements, or accelerated fetal growth and/or polyhydramniosShort term (< 24 h) admission for monitoring for hypertension, suspected preterm labour, or pre-labour rupture of the membranes

Such admissions are not AEs, but the underlying reason may be.

However, admission for other fetal or maternal issues, including IUGR, reduced movements, severe hypertension, seizures (eclampsia), antepartum haemorrhage, pre-term labour, pre-term premature rupture of the membranes (PPROM), psychiatric disorder, social issues, unstable lie/abnormal lie, amnioreduction, and other issues are to be reported as AEs, and may well be considered SAEs, especially if the admission is for > 24 h.

The following perinatal outcomes are pre-specified outcomes and will not be reported as AEs/SAEs:
NNU admissionPreterm delivery (< 37 completed weeks gestation)Meconium staining of the amniotic fluid or placentaNeed for phototherapyNeed for respiratory support – headbox oxygen

The following perinatal complications are to be reported as AEs and may be considered as SAEs:
Neonatal seizuresEncephalopathy treated with hypothermiaNeed for respiratory support – ventilation via an endotracheal tube or nasal CPAPSepsis requiring > 5 days antibiotics with symptoms or confirmed blood or cerebro-spinal fluid (CSF) culture

The period for safety reporting is from first dose of study treatment until 6 weeks post-delivery.

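### The time symptoms take to resolve after birth is a secondary outcome, but the stated maternal timepoints end at the birth admission, so resolution after discharge may go unrecorded

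*Protocol article*

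**What the plan says.** All references are to the protocol article.

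- **Secondary outcomes, maternal list.** The last item is how long symptoms take to resolve once the woman has given birth. A separate item covers days to resolution or amelioration of symptoms, so this one is specifically postnatal.
- **Secondary outcomes, timepoints.** Secondary maternal outcomes are evaluated one week after randomisation, at monthly visits up to 28 weeks, and finally "at weekly clinic visits after 28 weeks gestation and during admission for birth". The same sentence sets the evaluation "of the secondary neonatal outcomes at delivery and 1 week and 6 weeks after birth".
- **Secondary outcomes, primary outcome schedule.** The itch score is taken at one week, "then on a monthly basis up to 28^+ 0^ weeks gestation and then weekly to delivery".
- **Subsequent visits.** "The post-delivery outcome will be completed after delivery and before the woman leaves hospital". The section then adds: "Participants will be asked to attend for follow-up at 6 weeks postpartum, with routine blood samples". The bloods include bile acids and are drawn 1 to 3 days before the visit. The text does not mention symptoms or itch at that visit.
- **Expected events.** "The period for safety reporting is from first dose of study treatment until 6 weeks post-delivery".
- **Background.** On the course of symptoms, only "Maternal symptoms typically resolve after birth". No duration is given.

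**The concern.** The outcome times an event that starts at birth and may end after the woman has gone home. Every stated collection point for maternal outcomes or itch falls at or before hospital discharge. Postnatal timepoints appear in the same sentence, but only for the infants. A site following the text could close the item at discharge. A woman whose itch stopped on day 2 of a 3-day stay would then have a value, while one whose itch stopped on day 10 would have none, or would be entered as 3.

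Two features make the window matter for the comparison between arms. First, length of stay may vary with mode of birth, which is itself a secondary outcome, so the cut-off need not be the same in both arms. Second, the Interventions section describes different postnatal drug exposure. UDCA stops at birth or may be weaned at the clinician's discretion, while rifampicin is stepped down by 150 mg every 3 days. From 600 mg a day that is 600/150 = 4 steps, or roughly 9 to 12 days, much of which may fall after discharge. Any difference between arms in postnatal symptoms could therefore arise partly outside the window.

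**Working it through.** **Is there a figure to reproduce?** No. The article gives no time to resolution, no length of postnatal stay and no proportion unresolved at discharge. The first step is therefore a comparison of the text, and the second a sensitivity range on assumed inputs.

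**Step 1: the passages side by side.**

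| Item | Last stated point |
|---|---|
| Secondary maternal outcomes | Birth admission |
| Itch score | Delivery |
| Post-delivery outcome record | Before leaving hospital |
| Secondary neonatal outcomes | 6 weeks after birth |
| Maternal follow-up visit | 6 weeks; bloods described, symptoms not mentioned |
| Safety reporting | 6 weeks post-delivery |

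Maternal contact at 6 weeks is planned, but no visible sentence attaches this outcome to it.

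**Step 2: how much could be lost.** Assumptions, none from the documents: time to resolution is exponential with median m days; observation stops at discharge on day s, with s from 2 to 5; the alternative is observation to day 42. With rate λ = ln 2 / m, the share of women whose resolution is observed is

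p = 1 − exp(−λs).

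| True median m | s = 2 | s = 3 | s = 5 | s = 42 |
|---|---|---|---|---|
| 1 day | 75% | 87.5% | 97% | 100% |
| 2 days | 50% | 65% | 82% | 100% |
| 4 days | 29% | 41% | 58% | 99.9% |
| 7 days | 18% | 26% | 39% | 98% |
| 14 days | 9% | 14% | 22% | 87.5% |

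Example: m = 7, s = 3 gives λ = 0.0990 and p = 1 − exp(−0.297) = 0.257.

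**Step 3: what the analysed values would look like if unresolved women were dropped.** The median among those observed is −ln(1 − p/2)/λ. For m = 1 it is 0.7 to 1.0 days over s = 2 to 5, so there is little distortion. For m = 7 it is 1.0 to 2.2 days, a large one.

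The mean among those observed is 1/λ − s(1 − p)/p. At s = 3:

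- m = 7: 10.10 − 3 × 0.743/0.257 = 1.43 days, against a true mean of 10.1.
- m = 14: 20.20 − 3 × 0.862/0.138 = 1.46 days, against a true mean of 20.2.

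A true gap of 10.1 days in means would appear as 1.463 − 1.426 = 0.037, about 0.04 days.

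**Step 4: what happens if unresolved women are censored at discharge.** Under the same model the Kaplan-Meier median is correct when s ≥ m and not reached when s < m. It is not understated. The loss is then of information: with m = 7 or 14 the median is not reached for any s from 2 to 5. With status also obtained at day 42 it is reached in both cases.

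**The case against.** The case against has real force on several points.

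- **Table 1 is not shown.** The trial timeline is where a postpartum symptom check would normally appear, and the article condenses a fuller protocol. Absence from the visible text does not show that the trial omits the item.
- **The 6-week visit is more than a blood draw.** The samples are taken beforehand, so the woman then attends for follow-up. Adverse events are to be assessed at each study visit, and safety reporting runs to 6 weeks. A resolution date could be asked for there.
- **The timepoint sentence is not a closed list.** Bile acids are a secondary maternal outcome and are measured at 6 weeks, although that sentence does not include the visit.
- **The post-delivery outcome is undefined.** It may mean only the birth details.
- **Censoring belongs in the analysis plan**, and the Data analysis section defers detail to one.

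A reader might infer that the outcome is observed only in women whose itch stops before discharge, and that it is grossly understated. These points show that the documents support neither inference. The first ignores the planned 6-week contact and the unseen table. The second needs both a long time to resolution and a decision to drop or close out unresolved women, and the documents state neither.

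The mismatch itself survives. The possibility of asking at 6 weeks does not amount to a statement that it is asked. If Table 1 does list it, the timepoint sentence and the completion rule still need reconciling with the table. Nor can an analysis plan recover a date that was never collected. The Data analysis section names linear regression for continuous outcomes and no time-to-event method, so censoring cannot be presumed from the article.

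**Conclusion.** The concern holds as a mismatch between a listed outcome and the stated schedule. As written, the maternal timepoints cannot time a resolution that happens after discharge, so the outcome may be truncated at length of stay.

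The consequence runs from slight to severe depending on inputs the documents do not supply. It is small if the median is about 1 day (75-97% observed) and large if it is 7 or 14 days (18-39% and 9-22%), assuming exponential times and discharge between day 2 and day 5. Understatement, and the near-disappearance of a difference between arms, arise only if unresolved women are dropped or closed at discharge; with censoring the price is a median that may not be reached. The primary outcome is untouched. I rate this minor to moderate, confined to one secondary outcome.

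**What to change.** In the timepoint paragraph under Secondary outcomes, add the existing 6-week postpartum visit as a maternal timepoint for this outcome. At that visit record the date symptoms stopped, or that they have not. Under Subsequent visits, state that this item stays open after hospital discharge. Treat women unresolved at last contact as censored, not missing. Check that Table 1 agrees.

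Under the assumptions above, observation to day 42 would capture resolution in 98% of women at a 7-day median and 87.5% at a 14-day median. The cost is a sentence or two of wording and one or two eCRF fields at a visit already planned. The downside is some recall error in the date.

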## Main trial procedures (see timeline in Table 1)

### Informed consent

Written informed consent will be sought from the woman only after she has been given a full verbal explanation (by a healthcare professional or research midwife/assistant) and written description (via the most recent approved version of the PICF in the local national language). She will be given sufficient time to consider the information, and the opportunity to question the PI or other independent parties to decide whether she will participate in the trial. Women who do not speak English, or the national language if in a non-Australian centre, will only be approached if an interpreter is available.

**Table 1 Tab1:**
[figure not shown]
Trial Timeline

*GA* gestational age, *ALT* alanine transaminase, *LFTs* liver chemistry analysis, *INR/APTT* International Normalised Ratio/Activated Partial Thromboplastin Time

Notes to Table 1

^1^All screening assessments are part of normal clinical practice

^2^Bile acid samples need to be drawn shortly before a scheduled dose of UDCA, though fasting is not required. Women previously prescribed UDCA for treatment of mild ICP, and agreeing to randomisation, will have basal assessments performed 4–7 days after ceasing such therapy prior to randomisation into the trial

^3^Study treatment started after randomisation. Dose to be adjusted by PI if indicated by symptoms and/or blood tests taken during normal clinical practice

^4^Adverse events will be recorded from study entry until post-delivery discharge of woman and baby. All SAEs are to be reported to the Coordinating Centre within 24 h of Investigator knowledge

Women eligible for the trial, whether or not they participate, will be asked about their willingness to take part in a subsequent trial of planned delivery of such affected women at 36^+ 0^ weeks gestation compared with expectant management in terms of neonatal outcomes.

Women taking part in the study will be asked about any other drugs that have been prescribed or initiated after randomisation. If such medications include agents known to have a significant interaction with rifampicin, then a woman taking rifampicin will be asked to withdraw from the study, although any data obtained until withdrawal will be included, and any pregnancy outcome data will be recorded (with her consent).

Participating women will also be asked at recruitment about any antibiotics they may have taken in the 3 months prior to recruitment, as well as any progesterone supplements they may have taken.

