### Ursodeoxycholic Acid (UDCA)

There are no known drug contraindications to UDCA.

The starting dose of UDCA is 450-1000 mg daily (450 mg or 500 mg tablets as per local pharmacy stock to be taken once daily or twice daily), increased in increments of 500 mg per day every 3–14 days, if there is no biochemical/clinical improvement, up to a maximum of 2000 mg per day [32]. UDCA will be continued until birth and then discontinued, or it may be weaned at the discretion of the treating clinician.

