### Rifampicin

The dose of rifampicin is 300 mg twice daily. Administration of rifampicin will be withheld if, during treatment, there is a rise of serum ALT above 200 U/L, and the management of such patients discussed with senior clinicians, including CI [name] and/or CI [name], to decide about continuation of rifampicin therapy. Rifampicin will be weaned after birth by 150 mg every 3 days.

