### Procedures for recording AEs

Assessment for AEs are to be conducted at each study visit. All AEs occurring during the trial that are observed by the PI/delegate or reported by the participant will be recorded in the eCRF, whether or not attributed to the study drug. In recording the AE on the eCRF, whether the event was an SAE or not will be entered. All AEs determined to be an SAE must be reported following the guidelines and time frames below.

All AEs and SAEs will be followed-up to resolution with a start date and an end date recorded.

It will be left to the PI’s clinical judgement to decide whether or not an AE is of sufficient severity to require the participant’s removal from the trial. A participant may also voluntarily withdraw from treatment due to what she perceives an intolerable AE. If either of these occurs, the participant must be given appropriate care until symptoms cease or the condition becomes stable.

Unexpected serious adverse maternal and neonatal events (SAEs) will be reported to the sponsor within 24 h. The sponsor will forward these reports and their review of the SAE to the DSMC and the HREC that provided REC approval within 72 h of receipt.

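### The protocol gives two adverse-event windows that differ at both start and end, and does not say which governs; if discharge governs, events during the post-birth rifampicin wean could be missed

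*Protocol article*

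**What the plan says.** The protocol article states the period for adverse events twice.

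- Main trial procedures, note 4 to Table 1: "Adverse events will be recorded from study entry until post-delivery discharge of woman and baby". The same note asks that every serious event reach the Coordinating Centre within 24 hours of the investigator learning of it.
- Assessment and reporting of safety, Expected events: "The period for safety reporting is from first dose of study treatment until 6 weeks post-delivery".

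Three other places bear on which window is meant. Procedures for recording AEs says "Assessment for AEs are to be conducted at each study visit", and Subsequent visits says "Participants will be asked to attend for follow-up at 6 weeks postpartum". Trial outcomes places the last evaluation of the neonatal secondary outcomes at 6 weeks after birth.

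Treatment after birth is described separately for each drug. For rifampicin, "The dose of rifampicin is 300 mg twice daily" and then "Rifampicin will be weaned after birth by 150 mg every 3 days". For UDCA, "UDCA will be continued until birth and then discontinued", with weaning as an alternative if the treating clinician prefers it. Subsequent visits also lets the other trial drug be added in either arm once the allocated drug is at its maximum.

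On speed of reporting, Procedures for recording AEs has a second 24-hour rule: "Unexpected serious adverse maternal and neonatal events (SAEs) will be reported to the sponsor within 24 h".

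**The concern.** A site cannot obey both windows. One opens at study entry and the other at first dose. One closes when mother and baby go home and the other 6 weeks after delivery. Sites that resolve the conflict differently would collect events over different periods, and the counts would then reflect how a site read the protocol as well as what happened to its patients.

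The closing date matters more. Rifampicin has a planned taper after birth, whereas UDCA is stopped at birth or tapered at discretion. A window that closes at discharge could therefore leave out time on drug, and more of it in the arm under test. The trial is open label with about 54 women per arm. The DSMC reviews event listings every three months and assesses harm in each arm after 50 women, so a few missed events could matter to that comparison.

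**Working it through.** No sample size, power or event rate is involved. The check sets the windows side by side and counts days.

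**Comparison of the windows**

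| | Note 4 to Table 1 | Safety section |
|---|---|---|
| Start | study entry | first dose |
| End | discharge of woman and baby | 6 weeks (42 days) after delivery |

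One might treat the first as a window for recording and the second as a window for reporting. That does not reconcile them: an event in week 4 cannot be reported if recording stopped at discharge.

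**Length of the rifampicin wean**

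Inputs: 300 mg twice daily = 600 mg a day, for a woman still on the full dose at birth; a reduction of 150 mg every 3 days. The text does not say whether 150 mg comes off the daily total or off each of the two doses, or whether the first cut is made at birth or 3 days later. All four combinations are shown.

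- Off the daily total: 600 / 150 = 4 steps. Drug-free on day (4 − 1) × 3 = 9 if the first cut is at birth, or 4 × 3 = 12 if it is 3 days later.
- Off each dose: 600 / 300 = 2 steps. Drug-free on day (2 − 1) × 3 = 3, or 2 × 3 = 6.

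**Days lost if discharge closes the window**

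The documents give no length of stay, so the day of discharge, L, is an assumption and is varied. L is the later of the mother's and the baby's discharge. On-drug days unobserved = max(0, wean length − L). Days lost against the 6-week window = 42 − L.

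| L | Wean 9–12 days | Wean 3–6 days | Lost against 42 days |
|---|---|---|---|
| 2 | 7–10 | 1–4 | 40 |
| 5 | 4–7 | 0–1 | 37 |
| 7 | 2–5 | 0 | 35 |
| 14 | 0 | 0 | 28 |
| 21 | 0 | 0 | 21 |

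A window running to day 42 covers the whole wean on every reading, since the longest is 12 days.

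**The 24-hour rules**

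Note 4 covers all serious events and names the Coordinating Centre. Procedures for recording AEs covers unexpected serious events and names the sponsor, which then forwards them to the DSMC and the ethics committee. Scope and recipient both differ, so these could be two consecutive steps or one rule stated in two ways. The text does not settle it.

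**The case against.** The best reply is that the protocol, taken as a whole, leans towards 6 weeks. The dedicated safety section says so, adverse events are to be assessed at every visit, and there is a visit at 6 weeks. On that view note 4 is a loose footnote and nothing would be lost. Much of this stands: it makes the longer window the more natural reading. It does not remove the conflict, because note 4 is in force, no text ranks one statement above the other, and some text points the other way. Subsequent visits has the post-delivery outcome form completed before the woman leaves hospital, and Trial outcomes ends the listed maternal evaluations at the admission for birth. The body of Table 1 is not visible here, so it cannot be used to decide.

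A reader might go further and infer that harms will be under-counted in the rifampicin arm and that the DSMC's comparison will be biased. The documents do not support that, for four reasons:

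- It requires note 4 to govern, which is not established.
- It requires discharge to precede the end of the wean. The window runs until both mother and baby are discharged, and a long neonatal stay could outlast the wean.
- UDCA may also be weaned.
- Rifampicin may be added in the UDCA arm, so some of those women could be tapering it too.

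Nor do the two 24-hour rules plainly contradict each other, since they name different recipients.

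**Conclusion.** The inconsistency is certain: the two statements give different starts and different ends, and both cannot be followed. Its effect on the safety data is conditional. If sites close collection at discharge, 21 to 40 of the 42 post-delivery days are lost for discharge between day 21 and day 2. Unobserved time on rifampicin ranges from none to about 10 days, depending on length of stay and on how the wean is read. Any loss would fall mainly in the rifampicin arm, where a taper is planned for all, but not only there. These figures assume 600 mg a day at birth and a discharge day that the documents do not give.

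The primary outcome and its analysis are not affected. This is a drafting conflict that should be corrected because it governs safety data in an open-label drug trial in pregnancy. The 24-hour rules need clarification and are not shown to be in error.

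**What to change.** State one start and one end for adverse-event collection, identical in both arms, and use the same words in note 4 to Table 1 and in the safety section. Set the end at 6 weeks after delivery for mother and baby, with collection at the existing 6-week visit. For the start, choose either study entry or first dose and use it in both places.

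In the same amendment, say whether the 24-hour rule in note 4 (all serious events, to the Coordinating Centre) and the one in Procedures for recording AEs (unexpected serious events, to the sponsor) are consecutive steps or a single rule.

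The cost is amendment wording and a check that the eCRF accepts adverse events up to the 6-week visit. No new visit is needed. The dose and the wean are not touched.
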